## Methods and analysis

### Study design

The proposed study will be a three-group randomized control trial (RCT) design that includes 150 participants from Zhongda Hospital Affiliated to Southeast University, with equal allocation of participants to the three intervention groups. The research flow chart is shown in Fig. 1. The reporting of this protocol is strictly based on the Standard Protocol Items: Recommendations for Interventional Trials (SPIRIT), which is found in Additional file 1.

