### Sample size calculation

Previous studies showed that myofascial release therapy had notable effects [32] (corresponding to a Cohen’s *d* of about 0.5) on improving quality of life, prostate-related symptoms, and pain. The primary outcome will be the change in NIH-CPSI scores, the clinical response rate, and the remission rate as measured by the NIH-CPSI 4 weeks after the completed intervention. We assumed that extracorporeal shockwave combined with myofascial release therapy had similar effects on NIH-CPSI scores. A sample of 40 participants per group was computed by the G*power software to achieve a power of 60% and a level of significance of 5% and a 95% confidence level. To compensate for an estimated dropout rate of 25%, 150 participants will be ultimately required. (i.e., the number in each group is 50).

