### Statistical methods

Statistical analysts perform data analysis in a blind state. All statistics analyses will be performed using SPSS 25.0 for Windows (SPSS Inc., Chicago, IL, USA). All data will be entered into SPSS by the research assistant. A *p*-value of < 0.05 will be considered statistically significant. One-way (3 groups: single extracorporeal shockwave therapy vs single myofascial release therapy vs combined therapy) analysis of variances (ANOVA) with repeated measures will be performed to compare changes in sEMG assessment and NIH-CPSI scores between and within groups over different time points (i.e., T0-T2). A paired sample *t*-test was used to compare the differences in outcome indicators between groups at T2 and T3 to determine the long-term efficacy of each intervention. Post hoc analyses will be performed when any significant difference both between- and within-group is found in any of the outcome variables. Bonferroni correction will be used to adjust the alpha levels. Multilevel regression or a generalized estimating equation (GEE) will also be used as a sensitivity analysis to analyze the correlation between NIH-CPSI scores and the results of sEMG assessment of the pelvic floor muscle and the results of sympathetic skin response. Mediation analysis will examine the mediating effect of sEMG assessment at T1 on the relation between extracorporeal shockwave therapy and NIH-CPSI scores at T2. This study strictly controlled for gender, age, and BMI of the participants, which may affect the primary and secondary outcomes. The mean absolute difference (MAD) and standard error of measurement (SEM) will be used to evaluate inter-method reliabilities. Consequently, Bland–Altman plots will be used to investigate the agreement between NIH-CPSI and SSR. Since the two measurement results have different measurement units, a *Z*-score will be calculated based on the formula: *Z*-score = (observation value − mean value)/SD.

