It is now recommended by the British Urology Association that the main aim of CP/CPPS treatment is to mitigate functional damage to patients [42], usually with single internal and external fascia manipulation. However, most of the studies on myofascial release therapy are pre-and post-controlled trials while lacking high-quality randomized controlled trials [43]. As mentioned in the literature review, myofascial release therapy can effectively alleviate the symptoms of pelvic floor pain in patients, but evidence for the intervention efficacy remains greatly inconclusive because the main primary outcome in existing studies is subjective scale [32, 44, 45]. At present, there are no studies on myofascial release therapy combined with extracorporeal shockwave therapy. Our study will compare three treatments—single myofascial release therapy, extracorporeal shockwave therapy, and combined therapy—and then propose to compare the relationship between the three treatment modalities and the subjective and objective functional changes before and after treatment.

In previous assessments, we found that the symptoms of chronic pelvic pain syndrome may be closely associated with increased pelvic floor muscle tone, which can be effectively reduced with myofascial release therapy. In this study, by comparing the association between the primary and secondary outcome measure and different therapy modalities (extracorporeal shockwave, myofascial release, and combined therapy) on the therapeutic effect of pelvic floor hypertonia at T0-T3 stage, it was proposed to determine (1) if shockwave therapy can reduce pelvic floor muscle tension further after taking myofascial release therapy; (2) if the combined therapy can reduce pelvic floor muscle tone, relieve the discomfort symptoms, and improve the quality of life of the patients more efficiently and have a long-term effect than single treatment [46, 47]; (3) if curative effect can be reflected by the change of sympathetic skin response before and after treatment; and (4) if there exist other mechanisms that may improve the symptoms of patients other than what extracorporeal shockwave and myofascial release therapy did on reducing pelvic floor muscle tone.

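### The stated 60% power belongs to an unadjusted comparison with an effect never defined between arms; the Bonferroni-adjusted pairwise comparisons have about 42% to 48% even if that effect is granted

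*Protocol article*

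**What the plan says.** The section Sample size calculation in the protocol article begins from earlier work: "Previous studies showed that myofascial release therapy had notable effects [32] (corresponding to a Cohen’s *d* of about 0.5". Its next step is that "We assumed that extracorporeal shockwave combined with myofascial release therapy had similar effects on NIH-CPSI scores". It reports 40 participants per group from G*Power, "to achieve a power of 60% and a level of significance of 5% and a 95% confidence level", and then: "To compensate for an estimated dropout rate of 25%, 150 participants will be ultimately required", which is 50 per group. It names no test, no comparator for the d of 0.5, no difference between two arms of this trial and no multiplicity adjustment.

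The Study design section describes one randomised trial "with equal allocation of participants to the three intervention groups", and each of the three groups receives at least one active therapy. The Abstract says the trial will compare the efficacy of all three. The Discussion asks whether combined therapy will reduce muscle tone, relieve symptoms "and improve the quality of life of the patients more efficiently and have a long-term effect than single treatment".

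The Statistical methods section plans a three-group repeated-measures ANOVA, followed by post hoc analyses where a significant difference is found, and says "Bonferroni correction will be used to adjust the alpha levels". It does not give the number of comparisons.

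**The concern.** The sample size and the analysis do not describe the same comparison, in two respects.

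First, the effect size is the reported effect of one component therapy. The trial estimates differences between active arms: combined minus shockwave, combined minus myofascial release, and shockwave minus myofascial release. The section assumes a size for none of them.

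Second, the significance level in the calculation is a plain 5%, while the pairwise comparisons that would show which therapy is better are to be tested at a Bonferroni-adjusted level.

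At stake is how the result will be read. The Abstract says the trial is meant to select the most appropriate treatment option. A reader told that power was 60% would give a non-significant combined-versus-single comparison more weight than it deserves.

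**Working it through.** **Inputs from the protocol.** d = 0.5; 40 evaluable per group; power 60%; alpha 5%; dropout 25%; 50 enrolled per group (Sample size calculation). Three arms, 1:1:1 (Study design, Sequence generation). Bonferroni adjustment (Statistical methods).

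**Assumptions.** Two-sided tests. The number of comparisons is taken as three (all pairs, alpha 0.05/3 = 0.0167) or two (combined versus each single therapy, alpha 0.05/2 = 0.025). For the main figures the true difference between the two arms compared is set to 0.5 SD, which the protocol does not itself state.

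**Method.** Two-sample t-test with n per arm: noncentrality δ = d × √(n/2), degrees of freedom 2n − 2, power = P(|T| > critical value) under the noncentral t distribution.

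**Step 1: the protocol's own figure.** δ = 0.5 × √20 = 2.236, 78 degrees of freedom, alpha 0.05: power 59.8%. This reproduces the stated 60% with 40 per group. Other candidates:

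| Test | Power with 40 per group |
|---|---|
| Two-sided two-sample t, alpha 0.05 | 59.8% |
| Omnibus three-group F, one arm 0.5 SD above two equal arms (f = 0.236) | 62.1% |
| Omnibus F, f = 0.25 | 67.6% |
| Omnibus F, means evenly spaced over 0.5 SD | 49.3% |
| One-sided two-sample t | 71.6% |

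The first is the closest match, and the second is near enough that it cannot be excluded.

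**Step 2: the same difference at the Bonferroni level.** Power per pairwise comparison at d = 0.5:

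| Evaluable per arm | Alpha 0.05/3 | Alpha 0.05/2 |
|---|---|---|
| 37.5 (50 × 0.75) | 39% | 45% |
| 40 | 42.1% | 48.4% |
| 50 (no dropout) | 53% | 59% |

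Using the pooled three-group error with 40 per arm changes little: 42.7% and 48.8%.

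**Step 3: a smaller added benefit.** If combination adds 0.25 SD over a single therapy (an assumption), power with 40 per arm is 19.7% at 0.05, 12.7% at 0.05/2 and 9.8% at 0.05/3.

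**Step 4: detectable difference.** With 40 evaluable per arm at 0.05/3, 60% power needs d = 0.60 and 80% power needs d = 0.74.

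**Step 5: what a baseline covariate could recover.** Adjusting for the T0 score with baseline-to-follow-up correlation r divides the residual SD by 1/√(1 − r²), so the effective d is 0.5/√(1 − r²). The protocol gives no r. At alpha 0.025 and 40 per arm:

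| Assumed r | Effective d | Power |
|---|---|---|
| 0.3 | 0.524 | 53% |
| 0.5 | 0.577 | 62% |
| 0.7 | 0.700 | 80% |

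These still assume a raw between-arm difference of 0.5 SD.

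**The case against.** Several points on the other side stand.

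- **The t-test is inferred.** No test is named, and the omnibus F with one arm 0.5 SD above the other two gives 62.1%. On that reading the calculation would fit the planned three-group test. It would still rest on an unstated 0.5 SD advantage, and each adjusted pairwise comparison would remain at 42% to 48%.
- **A reader might infer that the authors assumed a zero difference between combined therapy and myofascial release.** The wording about similar effects allows that reading but does not require it; it can equally mean an effect of similar size, 0.5.
- **A reader might also infer that 0.5 cannot be a difference between any two arms.** That goes too far. The combined arm receives both treatments in the same format as the single arms, so if effects add, combined minus shockwave is the effect of myofascial release, possibly 0.5. The protocol does not state additivity, and this would not supply combined minus myofascial release.
- **A reader might want power for beating both single therapies.** At d = 0.5 for both and alpha 0.0167 that is about 27%, but the protocol sets no such success rule. The chance of at least one significant result of the two is about 59% at 0.0167 and 65% at 0.025.
- **The protocol is open about a low 60%.** True, but the point is that this figure does not describe the adjusted comparisons.
- **Repeated measures may add power.** Possibly, but the calculation states no correlation and claims no such gain.

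**Conclusion.** The concern holds in this form: the protocol states a power of 60% without the between-arm difference it refers to, at a significance level its own analysis section does not use for the pairwise comparisons. If the true difference is 0.5 SD, power per adjusted comparison with 40 evaluable per arm is about 42% (three comparisons) or 48% (two). The range across the protocol's dropout allowance and full retention is 39% to 53% for three comparisons and 45% to 59% for two. With 0.25 SD it is about 10% to 13% with 40 per arm. These figures rest on two-sided t-tests without covariate adjustment, and on a number of comparisons that the protocol leaves open. The documents do not show that the authors assumed no difference between arms, nor that the trial needs combined therapy to win both comparisons.

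**What to change.** Rewrite the sample size section so that it states:

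1. the assumed difference in NIH-CPSI between combined therapy and each single therapy, with its basis;
2. the number of pairwise comparisons and the Bonferroni-adjusted alpha that the statistical methods apply;
3. the resulting power for the evaluable number expected per arm, or the detectable difference (at 0.05/3 with 40 evaluable per arm, d = 0.60 for 60% and d = 0.74 for 80%).

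Specify adjustment of the NIH-CPSI comparison for the T0 score, which is already collected. The gain depends on a correlation the protocol does not give, so report it over a range.

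Limiting the confirmatory comparisons to combined versus each single therapy would move alpha from 0.0167 to 0.025 and raise power from 42% to 48% at d = 0.5 with 40 per arm. That is the sponsor's choice, because the Abstract and the Objectives section also compare the two single therapies with each other, and that comparison would become secondary.

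The cost is a text amendment and a less favourable stated figure. No extra patients are needed. Recruitment is under way, so the change should be made before the outcome data are analysed.

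### The 25% dropout allowance is miscalculated: 50 per group leaves 37 to 38 completers, short of the 40 the calculation requires

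*Protocol article*

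**What the plan says.** All the relevant figures are in the protocol article under Sample size calculation. The starting effect is taken from earlier work on myofascial release: "corresponding to a Cohen’s *d* of about 0.5". The base number follows: "A sample of 40 participants per group was computed by the G*power software", and its purpose is given as "to achieve a power of 60% and a level of significance of 5% and a 95% confidence level". The allowance for losses comes next: "To compensate for an estimated dropout rate of 25%, 150 participants will be ultimately required", with the clarification "i.e., the number in each group is 50".

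The outcome used for sizing includes the change in NIH-CPSI score, the clinical response rate and "the remission rate as measured by the NIH-CPSI 4 weeks after the completed intervention", so it is read at T3. The total of 150 is repeated in the Abstract and under Study design, the latter "with equal allocation of participants to the three intervention groups".

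**The concern.** The section names a requirement (40 per group), an expected loss (25%) and an enrolment figure said to make up for that loss (50 per group). The three do not agree. A dropout rate is a fraction of those enrolled, so the enrolment figure multiplied by 0.75 should return at least 40, and it does not.

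At stake is whether the trial delivers the power it claims under its own assumptions. A reader of a neutral result would take 60% power with 25% dropout as given, when the printed figures do not support it.

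**Working it through.** **Inputs** (all from Sample size calculation, except the number of groups, from Study design): required n = 40 per group; dropout = 25%; enrolled = 50 per group, 150 in total; d = 0.5; significance level 5%; power 60%; three equal groups. The test and its sidedness are not stated.

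**Step 1. Reproduce the 40.** For a two-sided comparison of two means, the normal approximation is

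n = 2 × (z₀.₉₇₅ + z₀.₆₀)² / d² = 2 × (1.960 + 0.253)² / 0.25 ≈ 39.2, rounded up to 40.

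The exact t-test solution is 40.2, with 59.8% power at 40 per group. A one-sided test would give 29, which does not fit. The stated 40 is therefore the output of a two-sided two-sample t-test, to rounding.

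**Step 2. Reproduce the 50.**

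- n × (1 + dropout) = 40 × 1.25 = 50 per group; × 3 = 150. This matches the protocol exactly.
- n / (1 − dropout) = 40 / 0.75 = 53.3, so 54 per group; × 3 = 162. Inflating only the total gives 120 / 0.75 = 160.

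The article does not print the step it used. Of the two formulas, only the first returns 50 and 150, and no rounding turns 53.3 into 50.

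**Step 3. What 50 per group delivers.**

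- Completers: 50 × 0.75 = 37.5 per group; 150 × 0.75 = 112.5 in total, against 120 required.
- Dropout rate that 50 per group covers: 1 − 40/50 = 20%.
- If patients drop out independently at 25%, the probability that a given group of 50 keeps at least 40 is 26.2% (binomial). For all three groups it is 0.262³ ≈ 2%.

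**Step 4. Power at the reduced size.** Non-central t, d = 0.5, two-sided, non-centrality d × √(n/2):

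| Evaluable per group | Power at 5% |
|---|---|
| 40 | 59.8% |
| 38 | 57.6% |
| 37.5 | 57.0% |
| 37 | 56.4% |

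As an illustration only: with three pairwise comparisons, a Bonferroni level of 0.05/3 = 0.0167 gives 42.1% power at 40 per group and 39.3% at 37.5. Statistical methods names Bonferroni but not the number of comparisons, so the three is an assumption. The gap between about 60% and about 40% comes from the stricter level. The dropout slip accounts for about 3 points in either case.

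**The case against.** The strongest objection is that the effect is small: 2.5 patients per group and under 3 points of power at 37.5 per group, in a trial that already accepts 60%. That is correct, and it limits the weight of the point without removing the error.

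A second objection is that not every dropout is lost to analysis. Criteria for discontinuing or modifying allocated interventions and Strategies to improve adherence to interventions both keep data already collected, and the repeated-measures ANOVA under Statistical methods covers T0 to T2. A patient lost only between T2 and T3 would still contribute there, so 37.5 is not necessarily the evaluable number for that analysis. This stands in part. The trial is sized on the NIH-CPSI four weeks after treatment, however, and earlier data supply no value at that visit. The text also presents the extra patients as compensation for dropout.

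Third, the power percentages depend on a test that the article does not name. That also stands, and they should be read as conditional on the t-test that reproduces 40. The shortfall in numbers does not depend on it, since it uses only 40, 25% and 50.

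**Conclusion.** The statement is wrong as written. At the protocol's own 25% dropout, 150 enrolled leaves 37 to 38 evaluable participants per group, not 40. The shortfall is about 7.5 participants in total (120 − 112.5). That conclusion uses only printed figures and assumes that 40 is the number needed after dropout, which is how the text presents it.

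The cost in power is modest: from 59.8% to between 56.4% and 57.6%, on the assumption of a two-sided two-sample t-test at 5% with d = 0.5. The point should be corrected because the claimed compensation is not achieved, but it does not by itself put the design in question.

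**What to change.** Keep 150 and correct the sentence in Sample size calculation. The version that keeps the trial's own dropout estimate would read along these lines: with 50 randomised per group and 25% dropout, about 37 to 38 per group will be evaluable at the four-week follow-up, giving roughly 56% to 58% power for d = 0.5 at two-sided 5%. The test and its sidedness should be named in the same sentence. If power after Bonferroni adjustment is also quoted (about 39% at 37.5 per group), state that it assumes three pairwise comparisons.

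The alternative is to say that 150 provides 40 evaluable per group at 20% dropout. That is arithmetically right, but the article gives no basis for 20%, so it should be used only if the investigators can justify that rate.

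Enrolling 162 would meet the stated target at 25% dropout, but it is not needed to make the statement true. The cost of the correction is one sentence and a slightly lower stated power; enrolment and conduct do not change.

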### Patient and public involvement statement

After signing the informed consent, the patient will take part in the study as a subject. Patients should receive regular treatment and assessment according to informed consent.The research questions and outcome measures are developed according to the possible pathogenesis and previous studies.3.No form of recruitment was undertaken for this study.Patients and the public will not be involved in the design of this study.Patients and the public will not be asked to assess the burden of the intervention and time required to participate in the research.No recruitment advertisements will be published. Patients, who plan to receive the treatment, will be included in this study.The results will be published in a peer-reviewed journal upon study completion.

### Blinding

This study was a double-blinded, randomized, controlled trial. The subjects had no knowledge of the distribution. Therapists will not be involved in collecting data, and data managers will not participate in the intervention of patients.

#### Extracorporeal shockwave pseudo-therapy

A plastic film is placed over the treatment head, so the ultrasound waves cannot act on the treatment area.

#### Myofascial release group pseudo-therapy

Apply pressure only to pain-free points on the patient’s abdomen, using gentle movements to produce as little pain as possible.

### Statistical methods

Statistical analysts perform data analysis in a blind state. All statistics analyses will be performed using SPSS 25.0 for Windows (SPSS Inc., Chicago, IL, USA). All data will be entered into SPSS by the research assistant. A *p*-value of < 0.05 will be considered statistically significant. One-way (3 groups: single extracorporeal shockwave therapy vs single myofascial release therapy vs combined therapy) analysis of variances (ANOVA) with repeated measures will be performed to compare changes in sEMG assessment and NIH-CPSI scores between and within groups over different time points (i.e., T0-T2). A paired sample *t*-test was used to compare the differences in outcome indicators between groups at T2 and T3 to determine the long-term efficacy of each intervention. Post hoc analyses will be performed when any significant difference both between- and within-group is found in any of the outcome variables. Bonferroni correction will be used to adjust the alpha levels. Multilevel regression or a generalized estimating equation (GEE) will also be used as a sensitivity analysis to analyze the correlation between NIH-CPSI scores and the results of sEMG assessment of the pelvic floor muscle and the results of sympathetic skin response. Mediation analysis will examine the mediating effect of sEMG assessment at T1 on the relation between extracorporeal shockwave therapy and NIH-CPSI scores at T2. This study strictly controlled for gender, age, and BMI of the participants, which may affect the primary and secondary outcomes. The mean absolute difference (MAD) and standard error of measurement (SEM) will be used to evaluate inter-method reliabilities. Consequently, Bland–Altman plots will be used to investigate the agreement between NIH-CPSI and SSR. Since the two measurement results have different measurement units, a *Z*-score will be calculated based on the formula: *Z*-score = (observation value − mean value)/SD.

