### Eligibility criteria

Patients with hormone abnormalities are excluded because thyroid dysfunction and testosterone may affect prostate function and myofascial status.

Participants will be screened using the following criteria.

Inclusion criteria:According to the National Institutes of Health classification of prostatitis [29], all male patients meet the diagnostic criteria for chronic prostatitis type IIIB/chronic pelvic pain syndrome (pain in the bladder, groin, perineal area, genitalia or lower abdomen with no significant abnormalities on urological examination);Patients are aged 20–40 years;Patients with chronic pelvic pain lasting over 6 months;Patients sign the informed consent form.

Exclusion criteria:Patients with significant coagulation disorders, perineal anatomical abnormalities, hormonal abnormalities, and neurological abnormalities;Patients with an apparent cause of pelvic pain, such as a history of previous surgery, chronic infection, trauma, prostatitis, and epididymitis;Patients receiving other treatments during the study;Patients with any urethral pathology;Patients who have had closed lumbar injections and previous lumbar surgery within 6 months;Patients with other conditions causing pelvic pain;Patients with contraindications to physiotherapy;BMI > 22.9

Termination and shedding criteria:Other serious illnesses occur in the course of treatment;Poor patient adherence and failure to complete the full course of treatment.

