### Criteria for discontinuing or modifying allocated interventions

Patients receiving other treatments during the study will be excluded as exclusion criteria, but rehabilitation interventions will still be provided. Participants who experienced severe adverse events during the intervention will discontinue treatment, and the data that have been collected will be used for subsequent data analyses.

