### Strategies to improve adherence to interventions

Three groups of participants will be treated by specially trained therapists and the intervention process will strictly follow the study protocol. If the participant is not treated and evaluated at the specified time interval, the primary investigator will contact the participant to ensure that the intervention is proceeding rigorously. If the participant continues to be absent from the treatment as needed or firmly withdraws from the study, the relevant data that have been collected will be used for subsequent data analyses.

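### The planned repeated-measures ANOVA, as standardly run, excludes patients with an incomplete T0–T2 series, so the partial data the protocol promises to use do not enter the main arm comparison

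*Protocol article*

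**What the plan says.** **Data-use rules.**
- Criteria for discontinuing or modifying allocated interventions: for patients who stop after a severe adverse event, "the data that have been collected will be used for subsequent data analyses".
- Strategies to improve adherence to interventions: for patients who stay absent or withdraw, "the relevant data that have been collected will be used for subsequent data analyses".
- Eligibility criteria, under termination and shedding: "Poor patient adherence and failure to complete the full course of treatment". This pulls the other way, towards patients who finish.

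**Analysis (Statistical methods).**
- The between-arm comparison of both primary outcomes is an "analysis of variances (ANOVA) with repeated measures will be performed to compare changes in sEMG assessment and NIH-CPSI scores between and within groups". The visits it covers are T0, T1 and T2.
- T3 is handled separately: a paired-sample *t*-"test was used to compare the differences in outcome indicators between groups at T2 and T3".
- "All statistics analyses will be performed using SPSS 25.0 for Windows".
- Multilevel regression or GEE appears only as a sensitivity analysis of how NIH-CPSI relates to sEMG and sympathetic skin response.

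**Expected loss (Sample size calculation).** "To compensate for an estimated dropout rate of 25"%, the target of 40 per group is raised to 50.

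**The concern.** A repeated-measures ANOVA in its usual form (SPSS GLM) needs a value at every time point for each patient and removes the rest. A patient with T0 and T1 who misses T2 contributes nothing to the comparison, not even T1. The two data-use promises therefore cannot be met in the analysis where they matter most, and the only named method that accepts incomplete series is assigned to a different question.

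Two things are at stake. The first is precision, in a trial planned at only 60% power. The second is possible bias, because the T1 values that might explain who left are set aside. Loss that differs by arm is plausible here. Background describes physical and psychological discomfort from the rectal route, and Harm outcomes gives about a 15% chance of perianal pain with transrectal myofascial release. Only two of the three arms receive that treatment in active form.

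**Working it through.** **1. The plan's own figure.** Inputs from Sample size calculation: d = 0.5, α = 5% (two-sided assumed), power 60%. For a two-group comparison, n per group = 2(z₀.₉₇₅ + z₀.₆₀)²/d² = 2(1.960 + 0.253)²/0.25 = 39.2, so 40. The noncentral *t* gives n = 40.2, and power 59.8% at n = 40. The stated 40 per group reproduces. The 50 per group is 40 × 1.25.

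**2. Who is excluded.** The ANOVA uses T0, T1 and T2.
- Missing T0, T1 or T2: excluded.
- Missing T3 only: stays in the ANOVA and is lost only from the T2–T3 paired test.
- Stops treatment but attends T1 and T2: stays in, unless the termination and shedding rule is used to remove the patient.

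If all the dropout falls before T2: 50 × 0.25 = 12.5 per arm, or 37.5 of 150 in total. This is a ceiling.

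**3. Precision.** Two-group *t*-test, d = 0.5, two-sided 5%:

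| Patients per arm | Power |
|---|---|
| 37.5 (complete series only, at the ceiling) | 57.0% |
| 40 (plan's target) | 59.8% |
| 50 (all contribute full information) | 69.7% |

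A likelihood-based model would fall between the first and last rows. The last is an upper bound, because a patient lost after T1 carries only part of the information about T2.

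**4. Error rate of the planned ANOVA.** The documents give no dropout by arm, no reasons for dropout and no correlations between visits, so these are assumptions: no true difference, three arms of 50, 25% loss after T1 in each arm, loss related to response in one arm only, visit correlations of 0.5–0.7 (equal or autoregressive), SD 1.

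| What drives loss in the one arm | Group test | Arm-by-time test | Bias in T0–T2 change |
|---|---|---|---|
| Nothing | about 5% | about 5% | none |
| T1 level | 15–19% | 7–9% | none |
| T0–T1 change | not quoted | 15–17% | 0.11–0.21 SD |

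**5. Why the rows differ.** Let loss depend on D, and let the patients who remain in that arm have a mean of D shifted by δ standard deviations. The bias in the T0–T2 change is δ · cov(T2 − T0, D)/SD(D).
- D = T1 level: the covariance is r₁₂ − r₀₁. It is zero when the two correlations are equal, as in both structures used. With correlations of 0.4 and 0.7 the bias was about 0.07 SD.
- D = T0–T1 change, equal correlation r: the factor is √((1 − r)/2), which is 0.50 at r = 0.5 and 0.39 at r = 0.7.
- D = T0–T1 change, autoregressive: the factor is (1 − r²)/√(2(1 − r)), which is 0.75 at r = 0.5 and 0.66 at r = 0.7.

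The upper end of the simulated bias implies δ = 0.21/0.75 = 0.28. The lower end follows from the same δ: 0.39 × 0.28 = 0.11. With 25% lost, δ = 0.28 means the patients who leave lie 0.28 × 0.75/0.25 = 0.84 SD from their arm's mean on D. That is a strong link, and a weaker one gives proportionally less bias.

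**The case against.** The strongest case on the other side has four parts.

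- **The text does not contradict itself outright.** The data-use rules promise use in later analyses, not entry of every patient into the primary ANOVA. Partial data could serve descriptive summaries and the multilevel or GEE analyses of association. Exclusion of incomplete series is standard behaviour of the method and is not stated in the article. An analysis plan, not shown, could add imputation and reconcile the two. This stands, so the point is a mismatch between promise and named method and not a flat contradiction.
- **Bias is not established.** A reader might infer that the arm comparison will be biased. That needs loss related to response differently by arm, and the documents give no such figures. When dropout depended on T1 in the same way in two arms, the completers' T2 difference was −0.50 against a true −0.50. This stands.
- **Figures for raw T2 means do not describe the planned comparison.** A reader might size the bias from completers' T2 values alone. The plan compares changes from T0, and under T1-driven loss the change contrast was unbiased when correlations were equal. This stands for the change contrast. It does not clear the ANOVA as a whole, whose group and arm-by-time tests were still inflated.
- **The loss is a ceiling, and the set is not strictly treatment completers.** The 25% sits beside an outcome measured 4 weeks after treatment, which is T3, whereas the ANOVA ends at T2. This stands.

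None of this supplies a named arm comparison that uses partial series.

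**Conclusion.** The point holds as a mismatch that the named method creates. The protocol commits to analysing data from patients who leave, then fixes a main comparison that, as standardly run, cannot include those with an incomplete T0–T2 series. It is more than a detail left to an analysis plan, because a specific method has been chosen and a better one is available in the same software.

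- **Patients affected:** up to 12–13 of 50 per arm, reached only if all the planned dropout comes before T2.
- **Power:** about 57% at that ceiling, against at most about 70%, for a simple two-group comparison at d = 0.5.
- **Type I error:** near 5% if loss is unrelated to response. Under the assumed one-arm dependence it is 7–9% to 15–17% for the arm-by-time test, and 15–19% for the group test under T1-driven loss. Bias in the T0–T2 change, 0.11–0.21 SD, arises in these simulations only when loss follows the early change.

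The potential harm rests on assumptions about dropout that the document neither supports nor rules out. The change should be made, but the documents do not show that the planned result would be wrong.

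**What to change.** **Analysis.** Make the main arm comparison a linear mixed model for repeated measures (SPSS MIXED) with arm, visit, arm-by-visit and an unstructured covariance, using all available data from all randomised patients. Baseline can be a covariate. Alternatively, T0 can be an outcome with its mean constrained equal across arms, which also keeps patients lost before T1. Adding T3 to the same model would bring follow-up data into the arm comparison without requiring both T2 and T3. Add a sensitivity analysis for data not missing at random. Multiple imputation ahead of the ANOVA would also reconcile the text, but less directly.

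**Text.** Reconcile the termination and shedding criteria in Eligibility criteria, and the data-use statements in the discontinuation and adherence sections, with Statistical methods. State for each kind of early stop whether the collected values enter the main comparison. This concerns use of data only, not when treatment should stop.

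**Cost.** A change of wording and slightly more analysis work, with no new data and no new software. The model relies on a missing-at-random assumption, which should be stated. The change is best made before any unblinded data are seen.
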